## Abstract

**Background:**

Adjuvant endocrine therapy is a cornerstone in managing estrogen receptor–positive early breast cancer but may adversely affect metabolic health, including weight gain, insulin resistance, and dyslipidemia. These changes increase the risk of cardiovascular disease and may influence breast cancer outcomes. However, the timing and magnitude of early metabolic changes following endocrine therapy initiation remain poorly characterized. Conventional definitions such as metabolic syndrome rely on dichotomous thresholds and may lack sensitivity to detect early treatment-related metabolic changes, highlighting the need for refined assessment approaches.

**Objective:**

This prospective follow-up study aims to investigate early metabolic effects of initiating adjuvant endocrine therapy in women with estrogen receptor–positive early breast cancer and to compare conventional and expanded approaches to metabolic health classification.

**Methods:**

This single-center, prospective observational study was conducted at Aarhus University Hospital, Denmark. Women aged≥18 years with early-stage estrogen receptor–positive breast cancer initiating adjuvant endocrine therapy and without pre-existing diabetes were eligible. Metabolic health was assessed at baseline and after 3 months using biometric measurements (weight, waist and hip circumference, waist-to-hip ratio, and blood pressure) and non-fasting blood samples (plasma glucose; hemoglobin A_1c,_ (HbA_1c_); lipid profile; and estradiol). The 3-month follow-up was selected to capture early metabolic changes while aligning with routine clinical care to minimize additional visits and reduce selection bias. Metabolic health will be evaluated using two conventional measures and two extended, exploratory measures. Conventional measures are metabolic syndrome (MetS), defined as meeting ≥3 of 5 established criteria (blood pressure ≥130/85 mmHg, triglycerides >2 mmol/l, high-density lipoprotein cholesterol <1.295 mmol/l, waist circumference >88 cm, and plasma glucose >7.8 mmol/l), and the Metabolic Syndrome z score (MetS-Z), a continuous standardized composite of the MetS components. Additional extended measures are exploratory: the extended MetS, which expands the standard MetS definition by incorporating low-density lipoprotein cholesterol (>3 mmol/l), body mass index (≥30 kg/m²), waist-to-hip ratio (>0.85), and HbA_1c_ (≥42 mmol/mol), and the EMETA score, a standardized composite of the extended MetS components calculated using the same approach as the MetS-*z* score.

**Results:**

The study was funded in July 2024. Recruitment occurred between November 2024 and April 2025, and follow-up was completed in September 2025. Statistical analyses are planned for February 2026, with results expected to be published in summer 2026.

**Conclusions:**

This study is expected to provide insights into early metabolic changes following initiation of adjuvant endocrine therapy and evaluate different approaches to classifying metabolic health. The aim to inform future research by helping to identify patients at increased risk of cardiometabolic complications and adverse breast cancer outcomes, warranting confirmation and validation of expanded metabolic measures in longer-term, larger cohorts.

## Introduction

Breast cancer is both the most frequent type of cancer and the leading cause of cancer-related mortality among women [1]. As survival rates improve, currently up to 90% in developed countries, there is increasing attention to the long-term health of breast cancer survivors [1,2]. Estrogen receptor-positive (ER+) early (stage I-III) breast cancer (EBC) represents the most common subtype, and adjuvant endocrine therapy (ET) is a cornerstone of its treatment [3,4]. While ET has significantly reduced recurrence and mortality, its metabolic side effects have emerged as a growing concern in survivorship care [4-6].

ET may influence metabolic health through estrogen deprivation [5,7]. Estrogen plays an important role in metabolic homeostasis by promoting insulin sensitivity, regulating lipid metabolism, and supporting vascular function [8,9]. By blocking estrogen receptors (tamoxifen) or suppressing aromatase activity (aromatase inhibitors, AI), ET may disrupt normal metabolic regulation, promoting weight gain, insulin resistance, and dyslipidemia [5,10-13]. These changes are risk factors for cardiovascular disease (CVD), which represents a major noncancer cause of morbidity and mortality among breast cancer survivors [14]. Furthermore, obesity and metabolic syndrome (MetS) at diagnosis have been associated with increased risk of breast cancer recurrence and mortality [15-18].

Although ET is typically administered for several years, routine clinical follow-up is often concentrated around treatment initiation. This limits systematic long-term monitoring of metabolic health in routine care, which highlights the importance of characterizing early metabolic changes. A short-term follow-up allows evaluation of initial changes in weight, lipid metabolism, and glycemic markers that may signal early metabolic vulnerability. A 3-month timeframe balances biological relevance with clinical feasibility, aligns with standard follow-up practice at the study site, and supports broad inclusion while minimizing selection bias.

Metabolic health is traditionally assessed using MetS, a dichotomous classification that identifies individuals as metabolically unhealthy when at least three of five criteria are met: hypertension (blood pressure ≥130/85), hypertriglyceridemia (triglycerides >2 mmol/l), low HDL (HDL <1.295 mmol/l), central obesity (waist circumference >88 cm), or hyperglycemia (plasma glucose >7.8 mmol/l) [19]. However, this binary approach may overlook subtle or early metabolic changes that do not meet clinical thresholds. [19,20]. An established alternative is the Metabolic Syndrome *z* score (MetS-*z* score), a continuous composite measure of standardized MetS components and widely used in research to assess metabolic health along a continuum [21-24]. However, both MetS and MetS-Z omit several cardiometabolic indicators relevant to breast cancer survivorship, including low-density lipoprotein (LDL), hemoglobin A_1c_ (HbA_1c_), BMI, and waist-to-hip ratio (WHR) [13,25,26]. To address this limitation, this study introduces two expanded measures of metabolic health, for exploratory and hypothesis-generating purposes: An extended MetS definition and the EMETA score, a dichotomous classification and a composite *z* score using the same approach as the MetS-*z* score, both incorporating the extended metabolic variables.

The aim of this study is to evaluate the early impact of initiating adjuvant endocrine therapy on metabolic health in women with ER+ EBC and to compare conventional and expanded approaches to classify metabolic health.

## Methods

### Study Population

This prospective, single-center observational study enrolled 112 patients with ER+ EBC who initiated adjuvant ET. Over a six-month period from November 2024, participants were recruited from the Department of Oncology, Aarhus University Hospital (AUH), Denmark. Patients were invited to participate during the consultation ET was prescribed. Participants received usual care throughout the study.

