### Eligibility Criteria

Patients were eligible if they met the following criteria: age ≥18 years, diagnosis of invasive ER+ EBC, and initiation of adjuvant ET. Up to three days of ET treatment were allowed, to allow for the timeframe of informed consent.

Patients were excluded for enrollment in case of pregnancy or lactation, pre-existing diabetes (type I or II), more than three dispenses of ET, or any psychological, familial, sociological, or geographical conditions potentially hampering compliance with the study protocol and follow-up schedule. These conditions were discussed with the patient before trial registration. Patients with pre-existing diabetes were excluded because their chronic metabolic dysregulation and glucose-lowering treatments could confound assessment of early metabolic changes. Patients were excluded if metastatic breast cancer was diagnosed in the period between study inclusion and the 3-month follow-up. As the study did not involve any intervention administered by clinical staff beyond routine care, there were no additional eligibility criteria for sites or individuals delivering interventions.

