### Exposure

The exposure of interest was initiation of ET over a 3-month period. ET consisted of either tamoxifen (20 mg daily) or an AI (letrozole 2.5 mg daily or exemestane 25 mg daily), prescribed according to standard clinical practice.

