#### Covariables

Information on the following co-variables has been collected from medical records and will be included in adjusted analyses. These include patient demographics: age, weight, height, Carlson Comorbidity score (0, 1‐2, 3‐4, ≥5), current comorbidities (none, cardiopulmonary disease, neurological, dyslipidemia, musculoskeletal, other cancers, abdominal, urogenital, endocrine, dermatological, others), smoking status (never smoker, former smoker, active smoker), civil status (living alone, living with a partner), and area of living (rural/city). Cancer-specific characteristics: date of breast cancer diagnosis, disease stage (T+N), human epidermal growth factor receptor 2 status, histological type, grade of malignancy, and previous breast cancer history. Treatment modalities included duration and type of neo-adjuvant and adjuvant therapy (including supportive prednisolone treatment), date of breast cancer surgery, and radiotherapy.

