### Analytical Approach

Statistical analyses will be conducted using Stata (version 18.5), with a 5% significance level for hypothesis testing. Changes in continuous primary outcomes (BMI and MetS-*z* score) will be analyzed using linear regression or linear mixed-effects models, as appropriate, to estimate mean within-person changes from baseline to 3-month follow-up. Changes in secondary continuous outcomes, including the EMETA score and individual metabolic parameters, will be analyzed using similar regression-based approaches. Changes in categorical outcomes (MetS and Extended MetS prevalence) will be analyzed using logistic regression models.

To account for exposure heterogeneity and treatment-related confounding, type of ET (tamoxifen vs aromatase inhibitor) and prior cancer treatments with potential metabolic impact, including neoadjuvant or adjuvant chemotherapy and supportive corticosteroid use, will be included as covariates in all adjusted analyses.

To address the secondary research question of whether certain patients are more vulnerable to early metabolic health deterioration following the initiation of ET, exploratory subgroup analyses will be conducted across both primary and secondary outcomes. These analyses will examine whether metabolic changes differ according to baseline and treatment-related characteristics, including age, BMI category, baseline metabolic status, menopausal status, type of ET, prior chemotherapy, smoking status, and comorbidity score. These subgroup analyses will be considered hypothesis-generating. Missing data will be assessed for randomness and extent. If data are missing at random, appropriate methods such as multiple imputation or mixed-effects models will be applied. Sensitivity analyses will be conducted to evaluate the potential impact of missing data on the study’s primary and secondary outcomes.

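### Other cancer treatment may overlap the baseline-to-3-month window; the plan does not mark it, so the mean change cannot be read as the impact of endocrine therapy alone

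*Protocol article*

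**What the plan says.** The Introduction sets a causal-sounding aim: "The aim of this study is to evaluate the early impact of initiating adjuvant endocrine therapy on metabolic health in women with ER+ EBC". The Objective in the Abstract likewise speaks of metabolic effects of starting endocrine therapy (ET). Under Exposure, "The exposure of interest was initiation of ET over a 3-month period", and ET is defined there as tamoxifen or an aromatase inhibitor. There is no comparison group. The models in Analytical Approach serve "to estimate mean within-person changes from baseline to 3-month follow-up".

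On other treatment during that interval:

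- **Study Population:** "Participants received usual care throughout the study".
- **Eligibility Criteria, inclusion:** "age ≥18 years, diagnosis of invasive ER+ EBC, and initiation of adjuvant ET". Nothing here asks that other adjuvant treatment be complete at baseline.
- **Eligibility Criteria, during follow-up:** the one cancer-related rule is "Patients were excluded if metastatic breast cancer was diagnosed in the period between study inclusion and the 3-month follow-up".
- **Analytical Approach:** the treatment covariates are type of ET (two levels) and "prior cancer treatments with potential metabolic impact, including neoadjuvant or adjuvant chemotherapy and supportive corticosteroid use".
- **Covariables:** "Treatment modalities included duration and type of neo-adjuvant and adjuvant therapy", together with supportive prednisolone, date of surgery and radiotherapy. The section says its variables enter the adjusted analyses and does not limit them to treatment given before ET.

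**The concern.** In a single cohort measured twice, everything that acts between the visits is part of the mean change. If some women also received other cancer treatment in those three months, and that treatment moves BMI or MetS-Z, the estimate describes a mix of treatments while the aim reads it as the impact of ET.

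The protocol accepts this kind of argument elsewhere: the Eligibility Criteria exclude pre-existing diabetes partly because its treatment could confound early metabolic change. No corresponding rule or analysis covers cancer treatment that overlaps the window. The limitations in the Discussion mention neither overlapping treatment nor the missing comparator.

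This is a different matter from earlier chemotherapy or corticosteroids, which Analytical Approach addresses. Here the other treatment would lie inside the measured interval. Both primary outcomes are affected.

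**Working it through.** **1. The plan's own figure.** Cohort Size gives n = 112, SD of BMI change 3, target change 0.8 kg/m² and a 5% level (two-sided assumed).

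- SE = 3/√112 = 0.283.
- Power = Φ(0.8/0.283 − 1.96) = 80.6%. With the noncentral t it is 79.9%.

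The stated power of above 80% is reproduced by a one-sample formula for paired change. This confirms that the design has no comparator. It says nothing about bias.

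**2. What the two covariate sections cover.**

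| Section | Treatment named | Time limit | Overlap with window marked? |
|---|---|---|---|
| Analytical Approach | ET type; chemotherapy, corticosteroids | Earlier treatment only | No |
| Covariables | Neoadjuvant and adjuvant therapy (type, duration), prednisolone, radiotherapy | None | No |

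Under either section, radiotherapy finished before baseline and radiotherapy given between the visits could receive the same code.

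**3. Does covariate adjustment remove the effect?** Let D be a woman's change, τ the mean change without co-treatment, C = 1 if other treatment overlaps the window, f the share with C = 1, and γ the extra change. The cohort mean of D is then τ + fγ.

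- Linear regression of D on covariates with an intercept: the residuals sum to zero, so the fitted change averaged over the cohort equals the crude mean, still τ + fγ.
- Mixed model with complete pairs and covariate main effects only: the time coefficient is again the mean paired difference, τ + fγ.

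Only an estimate at C = 0 isolates τ. That needs C to be defined, and neither section defines it.

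**4. Possible size for BMI.** The documents give neither f nor γ. Assumed for illustration: f = 10-40%, γ = 0.25-1.0 kg/m². Shift = f × γ.

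- Low end: 0.10 × 0.25 = 0.025 kg/m², which is 0.025/0.283 = 0.09 SE.
- High end: 0.40 × 1.0 = 0.40 kg/m², which is 0.40/0.283 = 1.4 SE and 0.40/0.8 = half of the target change.

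If the change without co-treatment were zero, the chance of a significant result would be Φ(shift/SE − 1.96) + Φ(−shift/SE − 1.96):

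| Shift (kg/m²) | Chance of a significant result |
|---|---|
| 0.10 | 6.4% |
| 0.30 | 18.5% |
| 0.40 | 29.2% |

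The SD of 3 refers to 3-5 years. If the 3-month SD were 1 (assumed), SE = 1/√112 = 0.094, and a shift of 0.10 would already give about 18.5%. No SD is given for MetS-Z, so no size can be put on that outcome.

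**5. What a restricted analysis would cost.** At SD 3 and a change of 0.8, using the formula in step 1:

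| Left out | n | Power |
|---|---|---|
| 10% | 101 | 76% |
| 20% | 90 | 72% |
| 30% | 78 | 65% |

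These figures assume that all 112 women have 3-month data.

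**The case against.** Several stronger readings are tempting, and the documents do not support them.

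- **That the plan handles only treatment given before ET.** Covariables commits adjuvant therapy and radiotherapy to the adjusted analyses without a time limit. What stands is that it differs from Analytical Approach on timing, and that neither section identifies overlap.
- **That overlap occurred.** No section reports it. Recording adjuvant therapy and radiotherapy does not place them between the visits. HER2 status is listed as a tumour characteristic; HER2-directed therapy and ovarian suppression are not mentioned anywhere.
- **That no planned analysis could reveal the problem.** The subgroup list is worded as open and includes treatment-related characteristics. It names earlier chemotherapy, however, and no stratum for concurrent treatment.
- **That the bias is large.** Both inputs are assumed, and the upper one (1.0 kg/m² extra) exceeds the whole target change. At the low end the shift is negligible.

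It can also be said that usual care is simply what an observational study observes, that parts of the text speak only of association, and that coding of covariates belongs in an analysis plan that is not shown. The first two points are fair, but the Objective and the Introduction still use the language of effects and impact. On the third, Analytical Approach takes up treatment-related confounding explicitly and states a solution confined to earlier treatment, while another section states something broader. That inconsistency is in the text itself.

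**Conclusion.** The point holds in a limited form. Eligibility and conduct rules leave room for other cancer treatment inside the window, the two covariate sections disagree on timing, and neither marks overlap. Because the primary estimate is an uncontrolled mean change, adjustment averaged over the cohort does not remove a co-treatment effect, so the result cannot be read as the impact of ET alone.

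The size and direction of any bias are unknown. The range of 0.03-0.40 kg/m² for BMI rests entirely on the assumed 10-40% and 0.25-1.0 kg/m², and on the stated SD for its comparison with a standard error of 0.28. If no participant had overlapping treatment, this bias is zero. The change is worth making because it is cheap and bears on both primary outcomes; it does not show the study to be invalid.

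**What to change.** Recruitment and follow-up are complete, and Results schedules the analyses from February 2026, so only analysis and wording can change. Before analysis starts:

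1. Reconcile Covariables with Analytical Approach on which treatments, over which period, enter the adjusted models.
2. Derive for each woman whether any cancer treatment other than the ET defined under Exposure overlapped the interval between her two visits. Use the extracted records, and check dates where only durations were recorded. Report the number with overlap.
3. Pre-specify one sensitivity analysis of change in BMI and MetS-Z limited to women without overlap. Report it with its confidence interval beside the full-cohort estimate.
4. Word the full-cohort result as change after ET initiation under usual care, whether or not the two estimates differ.

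The cost is one extra analysis and some checking of dates, with no new visits. The restricted group is smaller and its interval wider. It may also differ in stage and earlier treatment, so a gap between the two estimates would support a co-treatment effect but not prove one.

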### Eligibility Criteria

Patients were eligible if they met the following criteria: age ≥18 years, diagnosis of invasive ER+ EBC, and initiation of adjuvant ET. Up to three days of ET treatment were allowed, to allow for the timeframe of informed consent.

Patients were excluded for enrollment in case of pregnancy or lactation, pre-existing diabetes (type I or II), more than three dispenses of ET, or any psychological, familial, sociological, or geographical conditions potentially hampering compliance with the study protocol and follow-up schedule. These conditions were discussed with the patient before trial registration. Patients with pre-existing diabetes were excluded because their chronic metabolic dysregulation and glucose-lowering treatments could confound assessment of early metabolic changes. Patients were excluded if metastatic breast cancer was diagnosed in the period between study inclusion and the 3-month follow-up. As the study did not involve any intervention administered by clinical staff beyond routine care, there were no additional eligibility criteria for sites or individuals delivering interventions.

### Study Design

Participants underwent two metabolic health screenings: one at baseline and one at 3-month follow-up (Figure 1). The baseline screening was performed on the same day as study inclusion. The 3-month follow-up screening was performed on the same day as the 3-month ET follow-up. This design minimized additional study-related visits and supported participant retention.

**Figure 1. F1:**
[figure not shown]
EMETA study design and participation created in BioRender [27] is licensed under CC BY 4.0 [28]. AUH: Aarhus University Hospital.

### Exposure

The exposure of interest was initiation of ET over a 3-month period. ET consisted of either tamoxifen (20 mg daily) or an AI (letrozole 2.5 mg daily or exemestane 25 mg daily), prescribed according to standard clinical practice.

### Outcomes

The primary outcomes were selected to address whether initiation of ET is associated with early changes in overall metabolic health. Given the short-term follow-up and the aim to capture early, potentially subtle metabolic alterations, the primary outcomes include an anthropometric and a composite metabolic measure.

The primary outcomes are:

Change in mean BMI from baseline to 3-month follow-upChange in mean MetS-Z from baseline to 3-month follow-up

BMI was chosen because weight changes are a well-known sideeffect of ET and may occur early following ET initiation, representing a clinically meaningful marker of metabolic health. Although short-term changes may be modest, even small increases may indicate emerging metabolic vulnerability. As a continuous composite measure, the widely used MetS-*z* score was selected to capture multidimensional metabolic changes that may not be reflected by individual metabolic parameters alone [21-24,29].

Secondary outcomes were selected to further characterize early metabolic changes and to compare expanded and conventional approaches to metabolic health classification.

The secondary outcomes include:

Change in the prevalence of MetS from baseline to 3-month follow-upComparison of the prevalence of MetS and extended MetS at 3-month follow-upChange in mean EMETA score from baseline to 3-month follow-upChange in mean values of individual metabolic parameters from baseline to 3-month follow-up, including waist circumference, hip circumference, WHR, blood pressure, and circulating levels of HbA_1c_, total cholesterol, triglycerides, LDL cholesterol, HDL cholesterol, and estradiol

The extended MetS and EMETA score are included as exploratory outcomes to assess whether broader composite measures capture early metabolic changes not identified by conventional definitions. Analysis of individual metabolic parameters provides insight into which metabolic domains are most affected shortly after ET initiation.

